#### Moderators

In addition to the overall impact of PIM on children and mothers, we will also examine the differential impact of PIM on subpopulations of children and mothers based on poverty and health-related characteristics at baseline (e.g., MLH, adolescent mothers, women using alcohol, depressed women); i.e., we will test the moderating effects of these baseline characteristics. Separate models will be run for each moderator. The number of visits, ratings of the CHW supervisor on competency, content of the visits, skills used, frequency of phone contacts logged in real-time on mobile phones and verified by such systems as GPS, and random observations every 2 weeks are also moderators and will be analyzed in a similar fashion as above.

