#### AC

The CHWs in the AC will receive the initial Philani training as described above. In addition, the CHWs’ implementation will be consistently monitored and an accountability system will be established. In AC, supervisors will randomly observe home visits once every 2 weeks. CHWs in the AC will log their home visits on their mobile phones, including a rating of the content and skills addressed on the visit, children’s height and weight, and report on achievement of outcomes such as receiving the child grant, immunizations, breastfeeding, and retention and adherence to HIV care. The supervisors have two types of information, (1) personal observations of the CHW as they accompany the CHWs on their visits for 1 day every 2 weeks; and (2) reviewing data from a console as well as a folder which summarizes and documents every home visit made daily, the length of the visit, its location, the topics covered, the skills used by the CHW, and the perceived impact. The console reports also include the weight and length ratings of the child visited plotted on a growth chart. The supervisors do not change this information collected by the CHW on mobile phones, but merely review and use it for supervision and management of the CHWs. Supervision will facilitate CHW skill improvement over time. CHWs will be able to call mothers to check on illnesses such as diarrhea, provide reminders for immunizations and follow-up medical visits for HIV ARV or CD4 counts, as well as to make supportive calls to encourage depressed mothers to engage in pleasant events and a range of other motivating activities. Support, reminders, and monitoring will be the three primary functions that the supervisors will be encouraged to perform. Supervisors will not provide specific scripts or text messages for the CHWs. At each visit, the CHW enters a child’s weight and height in the mobile phone, which is translated into a WHO growth chart that both the mother and the CHW can review. The growth chart is brightly colored, clear, with a yellow color when the baby is in the desirable height-weight zone.

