There will be a “flag system” to prompt the CHW and supervisor when visits are due by the CHW and when a follow-up is needed. In addition to gathering real-time data on the health of the household, the mobile phone monitoring system automatically lists all follow-up visits needed for each week. For example, the CHW is expected to reach all households in their catchment area within a maximum of a 6-month period. Pregnant mothers are to be visited monthly and every 2 weeks within the last 6 weeks of pregnancy. A household with a severely malnourished or stunted child must be visited weekly. A household with a child within one SD of the normal height and weight only needs to be visited monthly. MLHs must be visited more often both in pregnancy and post-birth, especially if there has been no reengagement in care following childbirth (See Table 2).

**Table 2 Tab2:** Identification of responsibility for administrative and implementation functions with community health workers (CHWs)

	Standard Care	Accountable Care
Hiring	Local government	Local government
Salary	Local government	Local government
Training	Initial Philani Intervention Model (PIM) training	Initial PIM training and mobile phones provided
Visit documentation	Log sheet	CHW will log home visits in real time on mobile phones and enter information about the pregnant women in a folder for follow up purposes
Supervision	Local government	PIM
Type of supervision	Log sheet	Random supervision visits every 2 weeks including real-time and data-informed feedback; support and reminders will be sent to CHW and supervisors via mobile phones (“flag system”)

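### Six delivery variables that arise after randomisation are planned as moderators; three, probably four, have no described Standard Care values, and the number of visits is open to bias

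*Protocol article*

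**What the plan says.** The Moderators section asks whether the intervention works differently in subgroups of mothers and children defined by poverty and health at baseline: "we will test the moderating effects of these baseline characteristics". On the models it says: "Separate models will be run for each moderator".

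The next sentence extends this to delivery. It lists "The number of visits, ratings of the CHW supervisor on competency, content of the visits, skills used, frequency of phone contacts" and closes with "random observations every 2 weeks are also moderators and will be analyzed in a similar fashion as above".

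The AC section shows where several of these variables come from: "In AC, supervisors will randomly observe home visits once every 2 weeks" and "CHWs in the AC will log their home visits on their mobile phones, including a rating of the content and skills addressed on the visit". The same section bases visit frequency partly on the child's condition: "A household with a severely malnourished or stunted child must be visited weekly". A child within one SD of normal needs only a monthly visit, and mothers living with HIV are visited more often, especially if they have not returned to care after the birth.

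For SC, Table 2 gives a log sheet for both visit documentation and supervision. The Primary outcomes section says that the government log shows hardly anything beyond the fact of a visit, and that the trial will not be able to improve it.

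**The concern.** A moderator of a randomised effect has to be fixed before the intervention can act on it. Arms are then comparable within each level of the moderator, and the arm-by-moderator term compares like with like. The baseline characteristics in the first half of the paragraph meet this condition. The six delivery variables do not, since each is produced while the intervention is delivered and most are products of the AC package itself.

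Two problems follow, for different variables. If a variable is recorded in AC only, there is no SC relation to compare with, so no interaction exists to be tested. If it is recorded in both arms but influenced by arm and by the family's health, conditioning on it compares different kinds of families across arms.

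The Primary outcomes section treats the question whether monitoring and data-informed supervision make a difference as central to the study. These analyses would naturally be read as showing which parts of accountability work, and as written they cannot show that.

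**Working it through.** The plan states no figure for these analyses, so there is nothing to reproduce. The check has three steps.

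**Step 1. Where each variable exists.**

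| Variable | AC | SC | Arm-by-variable effect |
|---|---|---|---|
| Fortnightly observations | AC section, Table 2 | None described | Not estimable |
| Visit content ratings | AC phone log | None described | Not estimable |
| Skills used ratings | AC phone log | None described | Not estimable |
| Supervisor competency ratings | Implied by the AC supervision system | None described; government supervisors exist, and the text is silent on ratings | Apparently not estimable |
| Phone contacts | Real-time phone logging described for AC | Conflict: the SC section gives every worker a phone, Table 2 lists phones under AC only | Uncertain |
| Number of visits | Phone log | Log sheet | Estimable, open to bias |

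**Step 2. Why AC-only data give no interaction.** Take Y = b0 + b1·A + b2·M + b3·A·M, with A = 1 for AC and M the delivery variable. Then b3 is the slope of Y on M in AC minus the slope in SC.

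- SC coded as 0: A·M equals M in every row. A check with 720 rows gave a design matrix of rank 3 out of 4, so b2 and b3 cannot be separated.
- SC left missing: all SC rows drop out. A then equals the intercept and A·M equals M. Only a within-AC slope is left.

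**Step 3. Number of visits: an illustration of the bias.**

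Inputs from the document: 900 households with 80% retention give 720, or 360 per arm; the arm effect is 0.21 SD.

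Assumptions, not in the document: a frailty score U (variance 1) with coefficient −0.5 on the outcome; visits V = g·U + noise of variance 1, with slope g allowed to differ by arm; a mean of 0.5 units more visits in AC; no effect of visits on outcome; no true interaction; no clustering. There were 2,000 simulated trials per row.

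Within an arm, the slope of outcome on visits is cov(Y,V)/var(V) = −0.5g/(1 + g²). The interaction is the AC slope minus the SC slope. For g = 0.5 in AC and 0 in SC this is −0.25/1.25 − 0 = −0.20. The arm coefficient at V = 0 becomes 0.21 + 0.5 × 0.20 = 0.31.

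| g in AC | g in SC | Interaction by formula | Mean simulated interaction | Rejected at nominal 5% | Mean arm coefficient (true 0.21) |
|---|---|---|---|---|---|
| 0 | 0 | 0 | 0.002 | 4.6% | 0.213 |
| 0.3 | 0 | −0.15/1.09 = −0.138 | −0.135 | 46.6% | 0.278 |
| 0.5 | 0 | −0.25/1.25 = −0.200 | −0.202 | 82.4% | 0.312 |
| 0.8 | 0 | −0.40/1.64 = −0.244 | −0.244 | 95.8% | 0.334 |
| 0.5 | 0.5 | 0 | −0.002 | 4.4% | 0.312 |

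With equal slopes the false interaction disappears, but the arm coefficient is still wrong once visits are in the model. By the same formula, if visits followed frailty only in SC, with slope 0.3, the false interaction would be +0.138.

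The document supports the premise. Height and weight below −2 SD and maternal adherence, including return to HIV care, are outcome indicators in Table 1, and the AC flag system uses closely related states to set visit frequency. The visit schedule in the SC section depends on pregnancy and child age only. How SC workers in practice respond to a poorly growing child is not documented.

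**The case against.** The strongest reply is that the section never uses the word interaction. A similar fashion could mean separate models within AC, which can be fitted, and the detailed model terms may stand in an analysis plan that is not shown. It is true that the model form is inferred. But the sentence ties these variables to the same analysis as the baseline moderators of the intervention's effect. A within-AC model would not be a moderator analysis; it would be an observational association between delivery and outcome. A later plan that followed the sentence would inherit the problem. The Mediators section does not repair it, since it deals with maternal behaviour only.

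A second reply is that these are secondary analyses. That stands and limits the weight of the point.

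Some stronger readings are tempting but not supported:

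- A reader might infer that five of the six variables have no SC counterpart. The article conflicts on SC phones, and the Primary outcomes section lists phone reports as a data source without limiting them to AC. Three are clear and a fourth is likely.
- A reader might take weekly against monthly visits as a fourfold bias. That is a ratio between two AC scheduling categories. Against the twice-monthly schedule in the SC section it is about twofold, and the share of children in the weekly group is not given. It measures no bias.
- A reader might conclude that more visits will look harmful. The net sign depends on any true benefit of visits and on SC practice, and the document gives neither.

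**Conclusion.** The point holds. All six delivery variables arise after randomisation and should not be analysed as moderators alongside baseline characteristics. For fortnightly observations, content ratings and skill ratings, and apparently for competency ratings, no arm-by-variable effect can be estimated from the data described. Phone contacts remain uncertain until the article settles who has phones. For the number of visits, an interaction or a conditional arm effect can be computed but is open to bias of unknown size and net direction. The simulated values show only that a difference between arms in how visits follow frailty is enough to create a false interaction; they rest on assumed slopes and are not a forecast for this trial.

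The conclusion assumes that the analysis intended is the effect of arm by level of the variable, which is the natural reading of the section. The primary AC–SC comparison and the baseline moderator analyses are unaffected. The paragraph should be changed, but the trial's main result does not depend on it.

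**What to change.** Restrict the Moderators section to characteristics fixed at baseline. Remove the six delivery variables from it and report them as implementation or fidelity measures: within AC where only AC has data, and by arm for the number of visits. Label any association between them and outcomes as non-causal. Reconcile the SC section and Table 2 on phones, so that it is clear in which arm phone contacts can be reported.

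Two alternatives look attractive but should not be adopted:

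- **Randomised arm as an instrument for visits.** AC also changes supervision, feedback, skills and reminders, so arm can affect outcomes other than through the number of visits.
- **Mediation adjusted for growth before each visit.** This needs visit-level growth in SC. The SC log does not hold it, and the independent assessors measure growth only at the scheduled assessments.

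The cost is rewording one paragraph, with no new data. The downside is that the trial gives up a claimed moderator test of the delivery components, which its design cannot support.

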#### Mediators

We will also use Structural Equation Models to examine three pathways, namely the extent to which the effect of PIM on child outcomes is mediated through maternal behavior (e.g., caretaking); the extent to which a direct (not mediated) effect of PIM on child outcomes is also present; and the direct effect of maternal behaviors on child outcomes.

#### Power calculations

The primary outcome is the single outcome measure which sums the number of significant individual outcome measures and calculates the number of tests necessary to indicate a significant difference. All individual outcomes are based on an alpha = 0.05. There is sufficient power of 0.8 to detect a small effect size of 0.21 overall omnibus test between the SC and AC by 24 months. An intraclass area correlation of 0.01 and 80% retention is assumed. For subgroup analyses whose sample size is 1/2 (1/3) of the full data set, there is power to identify effect sizes of 0.31 (0.38) for alpha = 0.05, power = 0.8, supporting the detection of medium-small or better effect sizes in subgroups of size 1/2 or 1/3 of the population. Longitudinal analyses of child data beyond two time points (i.e., more than 6 and 15 months) may add modest increases to the power. For analyses of mothers’ data, longitudinal analyses will be conducted over all pre- and post-natal time points and tests of level shift for these analyses should have greater power than for child analyses, which will tend to be over fewer time points.

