**Methods/Design:**

In the deeply rural, Eastern Cape of South Africa, CHW will be hired by the government and will be initially trained by the Philani Programme to conduct home visits with all pregnant mothers and their children until the children are 2 years old. Eight clinics will be randomized to receive either (1) the Accountable Care Condition in which additional monitoring and accountability systems that Philani routinely uses are implemented (4 clinics, 16 CHW, 450 households); or (2) a Standard Care Condition of initial Philani training, but with supervision and monitoring being delivered by local government structures and systems (4 clinics, 21 CHW, 450 households). In the Accountable Care Condition areas, the CHW’s mobile phone reports, which are time-location stamped, will be monitored and data-informed supervision will be provided, as well as monitoring growth, medical adherence, mental health, and alcohol use outcomes. Interviewers will independently assess outcomes at pregnancy at 3, 6, 15, and 24 months post-birth. The primary outcome will be a composite score of documenting maternal HIV/TB testing, linkage to care, treatment adherence and retention, as well as child physical growth, cognitive functioning, and child behavior and developmental milestones.

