### Data analysis

A composite score will be calculated based on measures from birth to 24 months post-birth, similar to our composite measure in our previous RCT in Cape Town [33, 34]. It will be a sum of assessments of the attainment (1) or not (0) of well-being from 10 indicators of MCH. Outcomes will be assessed as present (1) or absent (0). Base rates influence the number of significant outcomes needed on individual domains to yield a significant result. To examine overall differences between MCH outcomes in the SC in contrast to the AC, a single index summing the 10 indicators will be calculated as the sum of 1 s, reflecting a score above the median (e.g., on months of breastfeeding) or present (getting all immunizations, attending > 3 antenatal visits), or 0 s, reflecting a score below the median or not present (e.g., no child grant, no maternal HIV testing in pregnancy).

The primary analyses will examine cumulative change across multiple indicators of maternal and infant health. For outcomes only assessed at 24 months, differences between AC and SC conditions will be examined using random effects regression models to control for neighborhood clustering. Differences between outcomes assessed at baseline, 6, 15, and 24 months will be explored using multi-level models adjusting for repeated measures and neighborhood effects. Data analysis will be conducted using SAS software version 9.2 [50]. Linear regression will be used for continuous variables, and logistic regression and Poisson/negative binomial regression will be implemented for binary and count outcomes, respectively. Logistic regression will be used for longitudinal binary outcomes.

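### The primary outcome is defined in two incompatible ways, as a participant-level sum of indicators and as a count of significant tests, and the power figure is not shown for the count

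*Protocol article*

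**What the plan says.** Three places in the protocol article bear on the primary outcome.

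- **Abstract, Methods/Design:** "The primary outcome will be a composite score of documenting maternal HIV/TB testing", followed by further maternal and child domains. This is a score.
- **Data analysis:** "It will be a sum of assessments of the attainment (1) or not (0) of well-being from 10 indicators of MCH". For the overall comparison of Accountable Care with Standard Care, "a single index summing the 10 indicators will be calculated as the sum of 1 s". This is also a score, one per mother-child pair. The same paragraph contains a sentence that belongs to a different method: "Base rates influence the number of significant outcomes needed on individual domains to yield a significant result".
- **Power calculations:** the primary outcome is a single measure that "sums the number of significant individual outcome measures and calculates the number of tests necessary to indicate a significant difference". It continues: "All individual outcomes are based on an alpha = 0.05". Then comes the power figure: "There is sufficient power of 0.8 to detect a small effect size of 0.21 overall omnibus test between the SC and AC by 24 months". The article does not say which of the two definitions that figure covers.

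**The concern.** A sum of indicators gives one value per participant. The arms are compared on its mean, with sampling variation among participants and clusters. A count of significant outcomes gives one value per trial. It is built from ten p-values and judged against the number of significant results expected by chance. The unit of analysis, the test statistic and the null distribution all differ, so these are not two descriptions of one method.

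A reader cannot tell which test decides whether the trial succeeded. If both remain, the choice can be made after the results are known. The power statement stands directly after the counting definition, so it reads as support for a rule for which no calculation appears.

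**Working it through.** **Inputs from the article.** 450 households per arm (Setting); 80% retention, intraclass correlation (ICC) 0.01, alpha 0.05 per outcome, power 0.80 at effect 0.21 (Power calculations); 10 indicators (Data analysis). **Assumptions of this check.** Two-sided tests; the same correlation between every pair of indicators, since the article gives none; a required number of 2, 3 or 4 significant tests, since it gives none.

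**1. The plan's own figure.** Retained per arm: 450 × 0.80 = 360. For one continuous score without clustering, the detectable effect is (1.96 + 0.8416) × √(2/360) = 0.2088. Power at 0.21 is Φ(0.21 × √(360/2) − 1.96) = 0.804. So 0.21 is what a comparison of one score gives. With the stated ICC and design effect 1 + (m − 1) × 0.01, it is not reproduced:

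| Clusters | m = 720/clusters | Design effect | Power at 0.21 | Detectable effect |
|---|---|---|---|---|
| 37 CHWs | 19.5 | 1.185 | 0.735 | 0.227 |
| 8 clinics | 90 | 1.89 | 0.536 | 0.287 |

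That shortfall is a separate matter. Here it matters only that the figure has the form of a single-score calculation.

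**2. Error of the count rule, independent tests.** Binomial(10, 0.05): P(≥1) = 1 − 0.95^10 = 0.401; P(≥2) = 0.086; P(≥3) = 0.0115. The smallest threshold that holds 5% is 3.

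**3. Error with correlated tests.** All indicators come from the same mother-child pairs in the same eight clinics, so some correlation is likely. Simulating ten equally correlated normal test statistics with no effect gives P(≥3) of about 0.03 at correlation 0.3 and about 0.05 (0.051 to 0.052) at 0.5.

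**4. Power if the effect is on the sum.** Set the effect on the sum to 0.2088 (80% power, no design effect) and spread it evenly. With correlation ρ, each item then has effect 0.2088 × √((1 + 9ρ)/10). At ρ = 0.05 this is 0.2088 × √0.145 = 0.080. Simulation with a threshold of 3 gives:

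| Assumed ρ | Power of sum | Power of ≥3 of 10 | Trials where the two disagree |
|---|---|---|---|
| 0.05 | 0.80 | 0.29 | about 51% |
| 0.1 | 0.80 | 0.41 | about 40% |
| 0.2 | 0.80 | 0.57 | about 24% |
| 0.3 | 0.80 | 0.67 | about 15% |
| 0.5 | 0.80 | 0.78 | about 6% |

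At ρ = 0.5 a threshold of 3 is marginally above 5% error. A threshold of 4 (error 0.026) has power of about 0.70.

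**5. Power if 0.21 is the effect on every indicator.** Without a design effect, a threshold of 3 has power 0.9999 at ρ = 0, 0.994 at 0.2, 0.985 at 0.3 and 0.958 at 0.5 (0.93 with a threshold of 4). The ordering reverses: the count rule then has more power than the stated 0.80.

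**The case against.** The strongest reply is that the counting rule may be sound once fully specified. The article says the required number of tests will be calculated, which is a calibration step. The number, its null distribution and the treatment of correlation are details that a journal article can leave to an analysis plan. The Data analysis section also points to a similar composite in an earlier trial, which is not at hand. This stands: the absent threshold is not itself the fault.

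Two stronger readings are tempting, and the document supports neither.

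- **That the count rule has far less power than stated.** This is true only if 0.21 is the effect on the sum and the indicators are weakly correlated. The gap narrows as correlation rises, and it reverses if each indicator has effect 0.21. The article does not say which applies.
- **That the count rule has no controlled error rate.** A threshold of three keeps error at about 3% up to correlation 0.3 and near 5% at 0.5. The independence cut-off and the threshold of three are devices of this check, not statements in the article. The lowest power and the highest error also occur at opposite ends of the correlation range, so they should not be quoted together.

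The reply does not remove the contradiction. The article states both definitions and explicitly calls the second one the primary outcome.

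**Conclusion.** The contradiction is certain from the text. The Abstract and most of the Data analysis section define a participant-level score. The Power calculations section, echoed by one sentence in Data analysis, defines a trial-level count of significant outcomes. Under the assumptions above, with the effect evenly spread on the sum and a threshold of three, the two tests disagree in about 15% to 51% of trials at correlations of 0.3 to 0.05, and in about 6% at 0.5.

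The 80% power at 0.21 fits a single-score comparison at 360 per arm without clustering and is not shown for the count. Whether the count has less or more power than 80%, and what its error rate is, cannot be determined from the article. The figures in steps 2 to 5 are illustrations that depend on an assumed threshold and assumed correlations. Because this is the primary outcome, the definition must be settled before recruitment, which had not begun when the article was submitted.

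**What to change.** 1. Name one primary analysis: the between-arm difference in the participant-level composite score, from the model that accounts for clustering, at two-sided 0.05.
2. Delete the counting of significant tests from Data analysis and Power calculations, or label it descriptive.
3. Report the individual indicators as secondary, with estimates and confidence intervals.
4. State that the power figure refers to the composite score.

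Resolving the contradiction does not require restricting the score to the 24-month visit or prescribing the level of the model; those choices remain with the investigators.

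**Cost.** No data collection changes. If the score was always intended, the change is one of wording. If the count was the intended primary analysis, this replaces it, and the change should be recorded as such before recruitment starts.

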### Setting

The OR Tambo District is a rural, hilly area in the Eastern Cape of South Africa accessible on a 150 km paved road east from Umtata and north of East London, with very high unemployment. The area is ancient tribal land, with the tribe allowing only minimal industrialization. Zithulele Hospital serves 130,000 families with nine local clinics. To reach clinics, a patient must cover large distances of hilly terrain either by walking or using the expensive and infrequent mini bus taxis. Aerial maps provided information on the density of each potential study area.

With the support of the District Health Officer, the team has documented the catchment areas of each CHW assigned to eight clinics in the catchment area of Zithulele Hospital. Data on access to electricity (8% in the region), water tanks (16%), flush toilets (few), distance from the road and the local clinics, and hilliness was used to identify areas of about 200 households each. The areas were matched by UCLA and all CHWs at each clinic (3–5 per clinic) were randomized to either (1) the Accountable Care (AC) condition, in which the PIM supervision and training models will be implemented (4 clinics, 16 CHW, 450 households); or (2) Standard Care (SC) by existing government supervisors and CHWs implementing home visits (4 clinics, 21 CHW, 450 households). Risk of contamination is very low given it is a deeply rural region with vast distances between villages and even homes. Figure 2 outlines the design of the randomized controlled trial (RCT), with the planned follow-up assessments by an independent team of assessors.

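### The stated detectable effect of 0.21 at 80% power does not follow from 450 households per arm, 80% retention and ICC 0.01 with the cluster numbers the article shows: about 0.23 with 37 CHW areas, 0.29 to 0.35 with the eight randomised clinics

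*Protocol article*

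**What the plan says.** The Power calculations section of the protocol article gives the main claim: "sufficient power of 0.8 to detect a small effect size of 0.21 overall omnibus test between the SC and AC by 24 months". It names two adjustments: "An intraclass area correlation of 0.01 and 80% retention is assumed". On the significance level it says "All individual outcomes are based on an alpha = 0.05", without giving sidedness. For subgroups of one half (one third) of the sample it says "there is power to identify effect sizes of 0.31 (0.38) for alpha = 0.05, power = 0.8". Gains from more visits are mentioned as a possible extra: "Longitudinal analyses of child data beyond two time points (i.e., more than 6 and 15 months) may add modest increases to the power".

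The sample size and the unit of allocation are given elsewhere. The abstract says "Eight clinics will be randomized to receive either (1) the Accountable Care Condition". The Setting section gives the AC arm as "4 clinics, 16 CHW, 450 households", and the SC arm as 4 clinics, 21 CHWs and 450 households. It also says that the catchment area of each CHW was documented. The Data analysis section plans random effects for neighbourhood clustering. The number and size of the clusters behind 0.21 are not given.

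**The concern.** The wording says that 0.21 already allows for both clustering and attrition. A routine calculation with both gives a larger effect, whether the clusters are CHW areas or clinics. The value 0.21 reappears when the design effect is left out. The subgroup figures are also too large relative to 0.21 for all three to come from one design.

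This is the only power statement for the primary comparison. If it is too favourable, readers will think the trial more sensitive than it is to a small effect. The gap is modest with CHW areas as clusters and large at the level of the clinics, which the abstract names as the randomised unit.

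**Working it through.** **Inputs from the article.** Alpha 0.05, power 0.80, ICC 0.01, 80% retention (Power calculations); 450 households per arm, 16 + 21 = 37 CHWs, 4 + 4 = 8 clinics (Setting). Retained: 450 × 0.80 = 360 per arm, 720 in all.

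**Assumptions.** Two-sided test; effect size read as a standardised mean difference; equal cluster sizes; one catchment area per CHW.

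**Formula.** Detectable effect = M × √(2 × DE / n), with DE = 1 + (m − 1) × ICC, n per arm and m retained households per cluster. M = 1.960 + 0.842 = 2.802 (normal). From the non-central t, M = 2.881 on 35 df (37 clusters) and 3.367 on 6 df (8 clusters).

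**Reproducing 0.21.**
- 360 per arm, no clustering: 2.802 × √(2/360) = 0.209.
- 450 per arm, no attrition, 37 areas: m = 900/37 = 24.3, DE = 1.233, 2.802 × √(2 × 1.233/450) = 0.207.

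Each of these leaves out one of the two stated adjustments.

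**Both adjustments, 37 CHW areas.** m = 720/37 = 19.5, DE = 1.185.
- Normal: 2.802 × √(2 × 1.185/360) = 0.227. With t on 35 df: 0.234.
- Power at 0.21: 0.735 (normal), 0.711 (t).

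**Both adjustments, eight clinics, ICC 0.01 assumed for clinics.** m = 720/8 = 90, DE = 1 + 89 × 0.01 = 1.89.
- Normal: 2.802 × √(2 × 1.89/360) = 0.287. With t on 6 df: 3.367 × 0.1025 = 0.345.
- Power at 0.21: 0.536 (normal), 0.407 (t).

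**Range over an assumed clinic ICC.**

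| Clinic ICC | DE | Normal | t, 6 df |
|---|---|---|---|
| 0.005 | 1.445 | 0.25 | 0.30 |
| 0.01 | 1.89 | 0.29 | 0.35 |
| 0.02 | 2.78 | 0.35 | 0.42 |

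**What 0.21 would need.** With 360 per arm, a value below 0.215 needs DE ≤ (0.215/0.2088)² = 1.06. That is about 7 households per cluster, or at least about 103 clusters. The article shows 37 CHWs and 8 clinics.

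**Check against the subgroup figures.** The planned subgroups (for example mothers living with HIV, adolescent or depressed mothers) are defined by characteristics of the mother. If they are spread across clusters, each cluster contributes fewer women and DE falls. The detectable effect then rises by at most √2 = 1.41 for a half sample and √3 = 1.73 for a third. The plan's ratios are 0.31/0.21 = 1.48 and 0.38/0.21 = 1.81. Rounding does not close the gap: 0.2149 × 1.414 = 0.304, below 0.305, and 0.2149 × 1.732 = 0.372, below 0.375.

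**The case against.** **The number of areas is not stated.** The 37 is inferred from the CHW numbers, and the text also speaks of neighbourhoods and of areas of about 200 households. With 120 areas, the normal formula gives 0.214 with both adjustments in place. This stands: it would be too strong to say that 0.21 is impossible under the stated ICC and retention. But the article shows no such number, and that reading gives 0.30 and 0.36 for the subgroups, not 0.31 and 0.38.

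**The ICC is for areas, not clinics.** This also stands. At an assumed clinic ICC of 0.001 to 0.003 the detectable effect would be 0.218 to 0.235 (normal) or 0.262 to 0.282 (t, 6 df). The clinic figures depend on that assumption, though even these lower values stay above 0.21.

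**The test may be one-sided.** With 37 areas that gives 0.202 (normal) or 0.206 (t). The half-sample figure would then be 0.27 to 0.28 rather than 0.31, and the clinic figure would still be 0.255 to 0.289.

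**The calculation may already use two time points, or a different omnibus test.** The wording leaves room for this. But no correlation between visits is stated, and the longitudinal gain is described as something that may be added.

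A reader might draw three stronger conclusions, which the article does not support:
- *That the subgroup figures prove a CHW-area calculation.* The normal formula gives 0.308 and 0.372, and the t formula 0.317 and 0.382. Neither rounds to 0.31 and 0.38 together. The ratios show that the three figures are inconsistent, not how each was obtained.
- *That repeated measures cannot bring the detectable effect below about 0.24.* The floor of 2 × 0.01/4 for the between-clinic variance of the difference (3.367 × 0.0707 = 0.238) holds only when post-birth visits are averaged. The plan has a pregnancy assessment and tests of level shift for maternal data, and pre-to-post contrasts or baseline adjustment can remove stable clinic differences.
- *That the trial has at best even odds of detecting 0.21.* That describes roughly the clinic-level case. With CHW areas as clusters, power is 71 to 74%.

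**Conclusion.** The concern holds: as written, the power statement does not follow from the arm sizes, retention and ICC together with either cluster number the article shows. With CHW areas the detectable effect is about 8 to 11% above the stated one (0.227/0.21 = 1.08; 0.234/0.21 = 1.11). At the level of the randomised clinics it is 37 to 64% above (0.287/0.21 = 1.37; 0.345/0.21 = 1.64), provided the ICC of 0.01 carries over to clinics.

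The conclusion rests on a two-sided test of a standardised mean difference and on one area per CHW. It does not rest on detail being left out of a condensed article: the figure printed disagrees with the inputs and with the subgroup figures printed beside it. An unweighted, unclustered calculation on 360 per arm is the simplest match for 0.21, but that is an inference about its origin.

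**What to change.** In the Power calculations section:

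1. Replace 0.21 with the detectable effect for the randomised unit: eight clinics, 90 retained women each, design effect 1.89 at ICC 0.01, giving 0.29 (normal) or 0.35 (t, 6 df), with 41 to 54% power at 0.21.
2. Label the clinic ICC as an assumption and show its range: for ICC 0.005 to 0.02, 0.25 to 0.35 (normal) or 0.30 to 0.42 (t).
3. State the cluster unit, the number of clusters and the sidedness of the test, and define the effect size.
4. Recompute 0.31 and 0.38 on the same basis. With eight clinics and the normal formula, a half sample (m = 45, DE = 1.44) gives 2.802 × √(2 × 1.44/180) = 0.354, and a third (m = 30, DE = 1.29) gives 2.802 × √(2 × 1.29/120) = 0.411.
5. On repeated measures, say at most that averaging post-birth visits alone does not remove between-clinic variance. Do not state a fixed floor.

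The cost is one paragraph of wording and a less favourable figure. No extra participants are needed, and the article reports that recruitment had not begun at submission.
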